#### Quantitative Analyses

We will describe the percentage of clinic encounters at which (1) the CDS tools appeared to users at the intervention clinics, (2) users reviewed tool suggestions, and (3) the suggested care plan adaptations were enacted.

The primary trial outcomes are changes in the two CQMs expected to be affected by social risk–informed care: blood pressure control and HbA_1c_ control. Each CQM’s denominator will be defined according to which patients are eligible for that measure at the time of a clinic visit (eg, patients with diabetes are in the HbA_1c_ measure denominator) per national CQM measurement specifications [41]. Two-level hierarchical linear models [48-50] will be used to assess the impact of CDS tools on these outcomes. As these outcomes are binary, the generalized form of the hierarchical linear model with a log link and binomial distribution will be used. Textbox 1 shows other potential covariates; this list will be finalized based on the extent to which person-level covariates were balanced between the final intervention and control arms and will be included in the first level of the model representing the person level. The second level of the model, the CHC level, will include arm as an independent variable (control vs intervention) and a random effect for the intercept (ie, intercept-as-outcomes model). Population-averaged marginal proportions and associated 95% CIs will be calculated by arm, along with the difference between those proportions (ie, the marginal effect) and the associated 95% CI that incorporates the random effects (ie, differences between CHCs) and any included covariates.

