In secondary analyses, a repeated cross-sectional design will be used to assess the differential changes in the outcomes across time. A panel design is impractical in this population of CHC patients, so using repeated measures would result in a selective (eg, patients with stable and continuous care) and smaller sample. As we will be able to collect up to 18 months of data, we will subset the relevant patient subpopulations within clinics in 6-month increments and model time as a between-subjects effect in the model described above to evaluate the effectiveness for each outcome. More specifically, we will add time (6, 12, and 18 months) and the product of time and arm that represents their interaction in level 2 of the model. We will then calculate the population-averaged marginal proportions and associated 95% CIs by arm and time points, along with the marginal effects between arms within time points and between arms across pairs of time points (ie, differences-in-differences). Significant marginal effects between arms across time would suggest a differential change between the arms across time. As all secondary CQM outcomes (Textbox 1) are also binary, we will use the same approach to evaluate between-arm differences on these outcomes as for the primary outcomes.

Intent-to-treat analyses will be used to establish effectiveness at the population level and per-protocol analyses to assess the impact of the tools when used. For the primary analysis, depending on the size of the intraclass correlation (between 0.01 to 0.05), this study has at least 80% power to detect a 9%-17% difference in blood pressure control (n=343 per CHC; assuming baseline level of 60% blood pressure control calculated from OCHIN data) and a 10%-18% difference in HbA_1c_ control (n=214 per CHC; assuming baseline level of 34% HbA_1c_ control calculated from OCHIN data) between the intervention and control groups at a two-tailed α level of .05.

Primary and secondary analysis variables.

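### The over-time secondary analysis treats one patient's records in successive 6-month windows as independent, for a reason that applies only to a complete-case panel, so the error bars of its differences-in-differences are misspecified

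*Protocol article*

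**What the plan says.** All the relevant text is in the Quantitative Analyses section of the protocol article.

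- **Design over time:** "a repeated cross-sectional design will be used to assess the differential changes in the outcomes across time".
- **Reason for not using repeated measures:** "A panel design is impractical in this population of CHC patients, so using repeated measures would result in a selective" sample, the example given being "patients with stable and continuous care) and smaller sample".
- **Model:** the windows are 6 months long, and the plan will "model time as a between-subjects effect in the model described above to evaluate the effectiveness for each outcome". That earlier model has two levels, person and community health center (CHC). Its single random effect is the CHC intercept.
- **Added terms:** "we will add time (6, 12, and 18 months) and the product of time and arm that represents their interaction in level 2", which is the CHC level.
- **Contrasts:** arm differences within each window, and differences-in-differences between pairs of windows. A significant contrast across time is to be read as the arms changing differently.
- **Denominators:** "defined according to which patients are eligible for that measure at the time of a clinic visit", following the national measure specifications.

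No patient-level term and no CHC-by-time term is stated.

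**The concern.** Hypertension and diabetes are long-term conditions, so many patients will be seen in more than one window of an 18-month follow-up. The plan settles how they are handled: each appearance counts as a separate person. The reason given runs together two different things. A closed panel, restricted to patients present in every window, would indeed be smaller and would favor those who stay in care. A repeated-measures model need not be restricted in that way. With a patient random effect or a patient-level working correlation, someone seen once contributes one record and stays in the analysis.

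At stake are the error bars of the differences-in-differences. These are the contrasts the plan uses to say whether the arms diverge over time. Two omissions act on them in opposite directions: the missing patient link and the missing CHC-by-time effect.

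**Working it through.** **The plan's own figure.** The only computed figures in the section are the detectable differences for the primary analysis: 9%-17% for blood pressure and 10%-18% for HbA1c, at intraclass correlation (ICC) 0.01 to 0.05. Using two proportions with design effect 1 + (m - 1) x ICC, six clinics against six give 8.8 to 17.2 points (m = 343, 60% control) and 9.5 to 18.6 points (m = 214, 34% control), which match. With the planned 6 against 30 the detectable differences are smaller (6.9 to 13.6 and 7.3 to 14.2), so the claim of at least 80% power holds. These figures do not concern the over-time analysis, and this point leaves them untouched.

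**Inputs.** From the documents: 6 and 30 clinics, m = 343, 60% blood pressure control, ICC 0.01 to 0.05. Assumed, because the documents give no values:
- f, the share of patients seen in both windows
- rho, the within-patient correlation
- cluster autocorrelation, where a value below 1 means that clinics drift between windows
- 343 patients per clinic in each window

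**Step 1: overlap alone.** For a change between two windows, modeled SE / true SE = 1/sqrt(1 - rho x f).
- rho 0.3, f 0.5: 1/sqrt(0.85) = 1.085, so the SE is overstated by about 8%.
- rho 0.5, f 0.8: 1/sqrt(0.60) = 1.291, so the SE is overstated by about 29%.

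A simulation of the clinic-intercept model (a Gaussian approximation on the proportion scale, 2,000 runs per setting, no drift) agrees. Type I error of the difference-in-differences is 1.9% to 2.6% at f = 0.5, rho = 0.5, and about 1% at f = 0.7, rho = 0.6. The 18-month arm contrast stays at 4% to 6%.

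**Step 2: size of the SE.** On the proportion scale at ICC 0.01, the plan's variance for a difference-in-differences is 2 x 0.24 x 0.99/343 x (1/6 + 1/30) = 0.000277, so SE = 1.66 points. With f = 0.5 and rho = 0.5 the patient part is multiplied by 1 - 0.25 = 0.75, giving 0.000208 and SE = 1.44 points.

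**Step 3: clinic drift.** With cluster autocorrelation 0.8 at ICC 0.01, drift adds 2 x 0.24 x 0.01 x 0.2 x (1/6 + 1/30) = 0.000192. The true variance is 0.000208 + 0.000192 = 0.000400, so the true SE is 2.00 points. Type I error is 2 x [1 - Phi(1.96 x modeled SE/true SE)]. The table keeps f = 0.5 and rho = 0.5.

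| ICC | Cluster autocorrelation | True SE (points) | Type I, plan's model | Type I, patient term only |
|---|---|---|---|---|
| 0.01 | 1.0 | 1.44 | 2.4% | 5.0% |
| 0.01 | 0.9 | 1.74 | 6.1% | 10.5% |
| 0.01 | 0.8 | 2.00 | 10.3% | 15.8% |
| 0.05 | 0.9 | 2.61 | 22.0% | 28.8% |
| 0.05 | 0.8 | 3.41 | 34.8% | 41.6% |

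The simulated type I errors for the plan's model at the same settings are 1.9%, 5.6%, 9.7%, 22.2% and 35.4%. Without drift, the patient term alone repairs the interval. With drift, it narrows an interval that is already too narrow.

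**Step 4: turnover.** Start at 60% control with no true change. Assume that control status persists and that there are no newcomers. If 30% of uncontrolled and 20% of controlled patients leave in both arms, each arm moves to 0.48/(0.48 + 0.28) = 63.2% and the difference-in-differences is 0. Now change only the departure of uncontrolled patients in the intervention arm:
- 20% leave: 0.48/0.80 = 60.0%, a false difference of -3.2 points
- 25% leave: 0.48/0.78 = 61.5%, -1.6 points
- 35% leave: 0.48/0.74 = 64.9%, +1.7 points

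Both size and sign depend on assumptions that the documents do not supply.

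**The case against.** The plan can be defended on four grounds.

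- **Estimand.** Repeated cross-sections are a legitimate design for a visit-based quality measure. The share controlled among those attending in a window is that measure, and if more uncontrolled patients stay in care, a lower later share describes it correctly. This stands: the design is not at fault. The independence assumption and its stated reason are.
- **Turnover.** A reader might infer that turnover will be mistaken for a tool effect. The documents do not support that. Turnover that is equal in both arms cancels. Bias needs departure that depends on control status and does so differently by arm. With 6 clinics that agreed to take part against 30 that were never approached this is possible, but nothing in the text shows it. The candidate covariates, which include visits in the last year, could absorb part of it, although the list is not final and is to be settled by balance between arms rather than across windows.
- **Direction.** A reader might also infer that ignoring overlap produces false positives. It does the reverse for change contrasts. The risk of false positives comes from the missing CHC-by-time effect.
- **Reach.** This is a secondary analysis, and the primary arm comparison and its power are unaffected. That stands too.

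None of this rescues the stated reason for rejecting repeated measures, or the treatment of one patient's records as independent.

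**Conclusion.** The point holds for the modeling of time and for its rationale. Records of the same patient are treated as independent, and the reason given applies only to a complete-case panel. The differences-in-differences therefore carry misspecified error bars. Overlap alone makes them about 8% to 29% too wide under the assumed correlations and overlaps. Unmodeled clinic drift, at assumed cluster autocorrelation 0.8 to 0.9 with f = 0.5 and rho = 0.5, takes type I error to about 6% to 10% at ICC 0.01 and 22% to 35% at ICC 0.05. The net direction cannot be settled from the documents, because overlap, within-patient correlation and drift are not given. Bias from turnover is a possibility to monitor and not a demonstrated fault. The change is worth making because these contrasts carry the plan's conclusion about divergence between arms over time, and the repair is cheap.

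**What to change.** 1. Keep the repeated cross-sections, with every eligible patient in each window, and link records by patient.
2. Add both a patient-level term (a random effect nested in CHC, or a patient-level working correlation) and a CHC-by-time random effect. Alternatively, use cluster-robust variance at clinic level with a small-sample correction, given only 6 intervention clinics. Do not add the patient term alone.
3. Reword the rationale: a complete-case panel would be selective and smaller, whereas the linked model retains patients seen in one window only.
4. Report, by arm, the share of first-window patients seen in each later window, split by their first-window control status.

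Cost: analysis wording and two more variance components. No new data collection is needed, since all quantitative data come from one centrally managed EHR. The fit is more complex and may have convergence difficulty with the log link. The linked estimate removes turnover bias only if return to care depends on earlier status that was observed.

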### Randomization and Recruitment

All OCHIN clinics that provide primary care and have documented ≥200 social risk screenings (excluding the pilot clinics) will be identified. It is anticipated that approximately 60 clinics will meet these criteria. Eligible clinics will be randomized 1:1 to 1 of 2 groups: potential intervention or control. Clinics from the potential intervention group (n=30) will be recruited in random order until 6 agree to participate. In the study analyses, outcomes in these 6 intervention clinics will be compared with those in the control clinics (n=30). This approach allows for randomization between the intervention and control arms while eliminating the recruitment of CHCs to a study where some will receive no intervention (ie, only clinics that will receive the intervention will be contacted for recruitment). This method is possible as all OCHIN member CHCs agree that their EHR data may be used in research as part of their membership agreement.

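### The secondary time-by-arm model has only a clinic random intercept, so its differences-in-differences intervals omit clinic-specific drift and are likely too narrow

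*Protocol article*

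**What the plan says.** All references are to the protocol article, mostly its section Quantitative Analyses.

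- **Model for the primary outcomes.** It has two levels, person and clinic: "The second level of the model, the CHC level, will include arm as an independent variable (control vs intervention". Its one random term is "a random effect for the intercept (ie, intercept-as-outcomes model".
- **Time analysis.** "In secondary analyses, a repeated cross-sectional design will be used to assess the differential changes in the outcomes across time". Patients are grouped into 6-month increments, and the plan is to "model time as a between-subjects effect in the model described above". The additions are named: "we will add time (6, 12, and 18 months) and the product of time and arm that represents their interaction in level 2".
- **Contrasts.** Besides arm differences within each time point, the plan estimates marginal effects "between arms across pairs of time points (ie, differences-in-differences" with 95% CIs.
- **Interpretation.** "Significant marginal effects between arms across time would suggest a differential change between the arms across time".
- **Clinics.** Under Randomization and Recruitment: "outcomes in these 6 intervention clinics will be compared with those in the control clinics (n=30".

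The article names no random time slope, clinic-by-period effect, robust variance or small-sample correction for this analysis.

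**The concern.** Allocation is by clinic, so the error term for any arm contrast should reflect how clinics vary on the quantity being contrasted. For a difference in level, the random intercept does this. For a difference in change, it does not: each clinic's intercept enters both periods and drops out, exactly on a linear scale and approximately for marginal proportions. What remains in the standard error is patient sampling error.

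Clinics do not all move in parallel. The article itself points to reasons for uneven movement: pandemic-related changes whose persistence is unknown, incomplete social risk screening that determines who is analysed, and a mix of in-person, telephone and virtual visits. If 6 clinics drift by chance relative to 30, the specified model has nowhere to put that variation except the time-by-arm term. The plan would then read it as a differential change between arms.

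This is not a detail left to the statistical analysis plan. The article states the random structure and what is added to it.

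**Working it through.** **Plan's own figure.** The article states no error rate or between-period correlation for this contrast. Its detectable differences are given for the primary analysis and do not enter here. The reference point is the nominal two-sided 5%.

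**Inputs from the article:** 6 and 30 clinics; ICC 0.01 to 0.05; blood pressure control 60% with n=343 per CHC; HbA1c control 34% with n=214 per CHC.

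**Assumptions:**
- CAC, the correlation of a clinic's underlying level between two periods: 0.8, 0.9 or 0.95, with 1.0 meaning no drift.
- m, patients per clinic per 6-month window: either the full n, or n/3 (about 114 and 71) as a lower extreme.

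**Formulas,** for one difference-in-differences between two periods, with p the control rate:

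- Variance the model reports: V0 = 2·p(1−p)·(1−ICC)/m·(1/6+1/30)
- Variance from clinic drift: V1 = 2·ICC·p(1−p)·(1−CAC)·(1/6+1/30)
- Ratio: R = (V0+V1)/V0 = 1 + m·ICC·(1−CAC)/(1−ICC)
- Actual two-sided error: 2·[1 − Φ(1.96/√R)]

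**Worked case: blood pressure, m=343, ICC 0.05, CAC 0.8**

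- V0 = 2 × 0.24 × 0.95/343 × 0.2 = 0.000266, so SE = 1.6 points.
- V1 = 2 × 0.05 × 0.24 × 0.2 × 0.2 = 0.00096; V0+V1 = 0.001226, so SE = 3.5 points.
- R = 1 + 343 × 0.05 × 0.2/0.95 = 4.61; error = 2·[1 − Φ(0.913)] = 36%.

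**Actual error of a nominal 5% test**

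| Outcome, m per window | ICC | CAC 1 | CAC 0.95 | CAC 0.9 | CAC 0.8 |
|---|---|---|---|---|---|
| BP, 343 | 0.01 | 5% | 7.0% | 9.1% | 13.2% |
| BP, 343 | 0.05 | 5% | 15.5% | 24.2% | 36.1% |
| HbA1c, 214 | 0.01 | 5% | 6.3% | 7.6% | 10.1% |
| HbA1c, 214 | 0.05 | 5% | 11.7% | 17.9% | 27.7% |
| BP, 114 | 0.01 | 5% | 5.7% | 6.3% | 7.7% |
| BP, 114 | 0.05 | 5% | 8.6% | 12.1% | 18.7% |
| HbA1c, 71 | 0.01 | 5% | 5.4% | 5.8% | 6.7% |
| HbA1c, 71 | 0.05 | 5% | 7.2% | 9.5% | 13.9% |

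**Simulation check.** With 20,000 runs per setting, 6 v 30 clinics, three periods, no true effect and a linear-probability analogue of the model, the error for blood pressure at ICC 0.05 and m=343 was 24.4% (CAC 0.9) and 35.6% (CAC 0.8). For HbA1c with m=214 and CAC 0.8 it was 27.4%. When clinic-by-period variation was put in the error term, the rate was 4.5-5.3% in every setting.

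**Recurring patients.** Treating time as between-subjects also ignores patients seen in more than one window, which makes V0 too large. Assume 70% overlap and a within-patient correlation of 0.5, so V0 is multiplied by 1 − 0.35. With full n and CAC 0.9 to 0.8:

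| Outcome | ICC 0.01 | ICC 0.05 |
|---|---|---|
| BP | 5.0-9.1% | 21-34% |
| HbA1c | 3.5-6.0% | 14-25% |

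At ICC 0.01 the two errors roughly cancel; at 0.05 they do not.

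**The case against.** **The size rests on figures the article does not contain.** No CAC is given, and at CAC 1 nothing is wrong. The n per CHC is stated for the primary analysis, not per 6-month window. Rates of a quarter to a third for blood pressure need the top of the ICC range, CAC of 0.8 to 0.9 and full n in every window, all together. At ICC 0.01 the drift variance is only 0.35 (CAC 0.9) to 0.69 (CAC 0.8) of the patient-level variance for blood pressure, and patient overlap can offset it. This stands: a reader might infer that the analysis has a 25-35% false-positive rate, and the documents do not support that as a general figure.

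**The analysis is secondary.** The primary arm comparison keeps the clinic random intercept, and its CI is said to include differences between CHCs. The arm contrasts within a time point keep it too. The affected contrasts compare one post-activation period with another. This also stands. Because the article calls the primary outcomes changes in the quality measures, a reader might infer that the main result is compromised; the primary model as described contains no time term, so that does not follow.

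**Level 2 might mean the clinic-period.** Time varies within a clinic yet is placed in level 2. If the level-2 unit were the clinic-period, drift would be captured but the correlation between a clinic's own periods would be lost. The article names level 2 as the CHC, so the plain reading is the one used here. The wording still needs clearing up.

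None of this supplies the missing variance term.

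**Conclusion.** The point holds for the differences-in-differences between 6, 12 and 18 months. As specified, their CIs contain patient sampling error only and are too narrow whenever clinics drift differently and patient overlap does not offset it.

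Over CAC 0.8 to 0.95 and the stated ICC range, leaving overlap aside, the nominal 5% becomes about 7-36% for blood pressure and 6-28% for HbA1c with full n per window. With n split over three windows, it is about 12-19% and 9-14% at ICC 0.05 and CAC 0.8 to 0.9, and about 6-8% at ICC 0.01. CAC, window size and patient overlap are assumptions.

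This should be fixed, but as a fault in a secondary analysis. It is not a reason to doubt the primary between-arm comparison.

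**What to change.** Either of two changes to the time-by-arm analysis:

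1. Add a random CHC-by-period effect to the model and use between-clinic degrees of freedom for the change contrasts.
2. Compute each clinic's change between periods and compare those changes between arms. This held about 4-6% error in simulation. It avoids convergence problems in a binomial log-link model with an extra variance term. It also needs no separate patient effect, because overlap is already reflected in the observed spread of clinic changes.

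The second is simpler and suits repeated cross-sections. Whichever is chosen, state whether the level-2 unit is the clinic or the clinic-period, and how many patients per clinic are expected in each window.

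No new data are needed. The cost is wider intervals for the change contrasts: in the worked case, an SE of 3.5 points instead of 1.6.

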### Objectives

This paper describes the protocol for a National Institutes of Health (NIH)-funded study (COHERE; Contextualized Care in Community Health Centers’ Electronic Health Records; R01MD014886) designed to develop and test CDS tools that present care team members with a given patient’s social risk information and both recommend and facilitate care plan adaptations based on those risks. This study will test the hypothesis that providing CDS that alerts care team members to patients’ known social risks and recommends relevant care plan adaptations will result in improved health outcomes. This study’s focus is on hypertension and diabetes control; however, the results will have implications for a wide range of morbidities.

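### Each of two primary outcomes gets a full two-sided .05 under one hypothesis, with no stated rule for combining them

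*Protocol article*

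**What the plan says.** All references are to the protocol article.

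- **Objectives** states one hypothesis: a tool that shows care teams a patient's known social risks and "recommends relevant care plan adaptations will result in improved health outcomes". Hypertension and diabetes control are given as the focus.
- **Quantitative Analyses** says "The primary trial outcomes are changes in the two CQMs expected to be affected" by social risk–informed care, and the variables list (Textbox 1) puts blood pressure control and HbA1c control side by side as primary. Neither is ranked above the other.
- The same section plans marginal proportions by arm for these outcomes, "along with the difference between those proportions (ie, the marginal effect) and the associated 95% CI". A 95% interval for each outcome corresponds to a two-sided .05 test for each.
- The power statement covers both outcomes in one sentence: "this study has at least 80% power to detect a 9%-17% difference in blood pressure control" and "a 10%-18% difference in HbA_1c_ control", each "between the intervention and control groups at a two-tailed α level of .05".

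The article does not say whether one significant outcome is enough, whether both are needed, or whether one is tested before the other.

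**The concern.** Two tests at .05 serve one general claim. If a significant result on either can be reported as support for that claim, the trial has two chances to be wrong at 5% each, and the error rate for the claim exceeds the stated alpha. With co-equal outcomes and no rule, a result that is significant on one and not on the other can be read either way after the data are seen. What is at stake is the meaning of the trial's main conclusion in that mixed case.

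**Working it through.** **Inputs from the article**
- Two primary outcomes, each at two-sided .05 (Quantitative Analyses).
- Blood pressure: "n=343 per CHC; assuming baseline level of 60% blood pressure control calculated from OCHIN data".
- HbA1c: 214 patients per clinic, 34% baseline control.
- Intraclass correlation (ICC) 0.01 to 0.05.
- 6 intervention and 30 control clinics (Randomization and Recruitment).
- The correlation between the two test statistics is not given. I assume 0 to 0.9.

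**Step 1: the plan's own figures.** Normal approximation, unpooled variance, increase from baseline. Effective n per arm = clinics × m / (1 + (m − 1) × ICC), and the difference d is solved from d = (z for alpha + 0.842) × SE. At two-sided .05:

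| Clinics | Blood pressure (points) | HbA1c (points) |
|---|---|---|
| Stated in the article | 9 to 17 | 10 to 18 |
| 6 v 6 | 8.8 to 17.0 | 9.5 to 18.4 |
| 6 v 30 | 6.8 to 13.0 | 7.4 to 14.5 |

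The stated figures match an unadjusted .05 per outcome with 6 clinics per arm, roughly to whole-point rounding. That cluster count is inferred; the article does not say which it used. For the 6 v 30 design the stated figures are conservative.

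**Step 2: false positives if either outcome counts, with no true effect on either.**
- Independent tests, either direction: 1 − 0.95² = 9.75%.
- Independent tests, improvement only: 1 − 0.975² = 4.9%, against 2.5% for one test.
- Correlated tests, bivariate normal: 1 − P(|Z1| < 1.96 and |Z2| < 1.96), and 1 − P(Z1 < 1.96 and Z2 < 1.96) for improvement only.

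| Correlation | Either direction | Improvement only |
|---|---|---|
| 0 | 9.75% | 4.9% |
| 0.3 | 9.5% | 4.8% |
| 0.5 | 9.1% | 4.5% |
| 0.7 | 8.35% | 4.2% |
| 0.9 | 7.0% | 3.5% |

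**Step 3: does the power statement survive a threshold of .025?** The z for alpha is 2.241, so the multiplier is 2.241 + 0.842 = 3.083. With 6 v 30 clinics:
- Blood pressure, ICC 0.01: design effect 1 + 342 × 0.01 = 4.42; effective n 2058/4.42 = 465.6 and 10290/4.42 = 2328. With d = 0.074, SE = √(0.674 × 0.326/465.6 + 0.6 × 0.4/2328) = 0.0240, and 3.083 × 0.0240 = 0.074.
- The same calculation gives 14.2 points at ICC 0.05, and 8.2 and 15.9 points for HbA1c.

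All four are smaller than the stated 9, 17, 10 and 18 points. Power at those stated differences, in the same order, is 94%, 94%, 93% and 89%, or 92%, 92%, 91% and 87% with a t reference on 34 degrees of freedom.

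**The case against.** The strongest reply has three parts.

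- **Silence is not a rule.** The .05 stands in a power statement, not in a decision rule, and the success criterion may be in an analysis plan that is not shown. This stands in part. A reader might infer that the plan lets either outcome carry the hypothesis, but no sentence says so, and a both-must-succeed rule or a fixed order would hold the error at 5%. What the article does fix is two unranked primary outcomes and a full .05 for each, and that alone does not control the error of the shared hypothesis.
- **There may be two claims, not one.** The hypothesis speaks of outcomes in the plural, and each measure has its own denominator, interval and power figure. If they are reported as two separate questions, familywise control is a matter of judgement. But Objectives frames one hypothesis, so the reading that needs control is at least as natural.
- **9.75% counts apparent harm too.** This is correct. A reader might infer a nearly 10% chance of falsely claiming benefit; that chance is at most about 4.9%. It is still close to double the nominal 2.5%.

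A reader might also infer that the quoted power fails once alpha is split. The documents do not support this. At .025, power at the stated differences drops below 80% (to 69-76%) only with 6 clinics per arm, and the article specifies 6 v 30.

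**Conclusion.** The point holds as one about error control. With .05 on each of two primary outcomes and no rule joining them, the chance of at least one false positive is about 7% to 9.75%, or about 3.5% to 4.9% for false claims of improvement against a nominal 2.5%. These figures assume that either outcome would be accepted as support, that the tools affect neither, and that the correlation lies between 0.9 and 0.

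It does not extend to power. The claim of at least 80% power at 9-17 and 10-18 points remains true at .025 for 6 v 30 clinics under the article's own inputs.

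**What to change.** State the rule before outcome data are seen, in one of two forms:

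- **Holm across the two primary outcomes.** Test the smaller p-value at .025 and, if it is significant, the other at .05. The 95% intervals can still be reported, with the Holm result deciding significance.
- **Both must succeed.** Say so and keep .05 for each. The power that matters is then joint: 80% on each gives 0.80 × 0.80 = 64% under independence, so joint power should be quoted for the 6 v 30 design.

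Under Holm, add that the quoted differences keep at least 80% power at .025 with 6 v 30 clinics (7.4-14.2 and 8.2-15.9 points detectable by normal approximation). Do not raise the quoted ranges by the 10% that a change from .05 to .025 implies (3.083/2.802 = 1.10). They already exceed what this design needs, so raising them would overstate its detectable difference.

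The cost is a sentence or two and a slightly stricter first-step threshold. Clinics, data and the stated power are unchanged under Holm.
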